## Abstract

**Background:**

Genetic information given to an individual newly diagnosed with a genetic condition is likely to have important health implications for other family members. The task of communicating with these relatives commonly falls to the newly diagnosed person. Talking to relatives about genetic information can be challenging and is influenced by many factors including family dynamics. Research shows that many relatives remain unaware of relevant genetic information and the possible impact on their own health. This study aims to evaluate whether a specific genetic counselling intervention for people newly diagnosed with a genetic condition, implemented over the telephone on a number of occasions, could increase the number of at-risk relatives who make contact with genetics services after a new genetic diagnosis within a family.

**Methods:**

This is a prospective, multi-centre randomised controlled trial being conducted at genetics clinics at five public hospitals in Victoria, Australia. A complex genetic counselling intervention has been developed specifically for this trial. Probands (the first person in a family to present with a diagnosis of a genetic condition) are being recruited and randomised into one of two arms – the telephone genetic counselling intervention arm and the control arm receiving usual care. The number of at-risk relatives for each proband will be estimated from a family pedigree collected at the time of diagnosis. The primary outcome will be measured by comparing the proportion of at-risk relatives in each arm of the trial who make subsequent contact with genetics services.

**Discussion:**

This study, the first randomised controlled trial of a complex genetic counselling intervention to enhance family communication, will provide evidence about how best to assist probands to communicate important new genetic information to their at-risk relatives. This will inform genetic counselling practice in the context of future genomic testing.

**Trial registration:**

Australia and New Zealand Clinical Trials Register (ANZCTR): ANZCTRN12608000642381.

## Background

When an individual (proband) receives a new diagnosis of a genetic condition for themselves or their child, the genetic information often has implications for other family members who may themselves be at risk of carrying the same mutation. This means that they may develop the condition themselves or risk passing the mutation on to their children.

Current local practice in state funded health services in Victoria, Australia, in keeping with Victorian Privacy laws, is for genetic health care providers to discuss with the proband the importance of communicating the genetic information to at-risk relatives and offer resources such as letters or information sheets. The health care provider, however, does not make direct contact with relatives. Despite routine advice given to the proband about the importance of communicating risk to relatives, it is estimated that between 20 and 40% of at-risk relatives remain unaware of the relevant genetic information [1-3]. Several reasons have been identified for this failure of family communication. First, genetic information is often difficult to understand and to explain clearly, and probands may lack knowledge or confidence in their ability to communicate this information [4-6]. Further, while probands frequently describe feeling a sense of obligation about informing other at-risk relatives [7], they may be reluctant to do so due to existing challenging family dynamics and relationships [8,9]. Finally, probands may wish to protect their family members from anxiety [10-13] or they may be experiencing difficulties in coming to terms with their own diagnosis, [1,14] making communication problematic.

Most knowledge of how families communicate genetic information comes from research into families with inherited cancers. It is recognised that probands frequently deliberate about when may be an appropriate time for their relatives to receive the genetic information [15]. Women are more likely to communicate than men [16] and, when communication occurs, it appears that first-degree relatives are usually informed first and often with an assumption that those who are informed will in turn pass the information on to their close relatives [1].

When questioned about how communication of genetic information should optimally occur, relatives believe that it should be done by family members but supported by genetic health professionals [12]. Health professionals themselves have often debated whether they should take a more active approach in informing possibly at-risk family members about genetic information. Professional guidelines encourage discussion of the importance of family communication [17] and there have been some attempts by genetics services to assist probands to do so by asking for contact details and sending letters to at-risk relatives on their behalf [18] or by use of a genetic register [19].

Overall, it appears that probands require more assistance to communicate genetic information effectively [6,20]. A small study in Australia provided evidence that additional genetic counselling support could result in a significant increase (36-61%) in family communication, represented by an increase in contact from at-risk family members with genetics services [19].

## Presentation of the hypothesis

The aim of this multicentre randomised trial is to investigate whether a specifically designed genetic counselling intervention will result in increased access to genetics services by at-risk family members, following identification of a genetic condition or carrier status in a proband.

The main hypothesis is that a specifically designed genetic counselling intervention delivered by phone at three time points over 18 months will facilitate communication of important genetic information within families, thereby increasing the number of at-risk family members who seek information and/or testing from genetics services.

## Testing the hypothesis

The following details are presented in accordance with the CONSORT reporting guidelines for randomised trials of non-pharmacologic treatment [21]. The following Human Research Ethics Committees in Victoria, Australia have all approved this project: Austin Health, Bendigo Health, Ballarat Health, Royal Childrens Hospital, Melbourne Health and Southern Health.

### Participants

#### Inclusion criteria

Potential participants for this prospective, randomised controlled trial must:

• be the first person in a family to be diagnosed, or have a child diagnosed, with a genetic condition about which the genetic information has implications for other family members and for which genetic testing or diagnosis based on clinical information is possible

• be able to speak, read and write English

• have at least one at-risk relative who resides in Victoria

• be aged 18 years or over.

#### Exclusion criteria

Potential participants are excluded if they:

• have a cognitive disorder that affects their ability to give informed consent

• have received a diagnosis during pregnancy

• reside outside of Victoria.

#### Setting and locations

The trial is being conducted within genetic clinic settings at six tertiary public hospitals in Victoria. These sites were chosen on the basis of variation in client populations and types of genetic diagnoses likely to be made, as well as the presence of an experienced genetic counsellor on staff.

#### Genetic counsellors performing the intervention

The 10 genetic counsellors in the study routinely disclose new genetic information to probands as part of their clinical duties. Each genetic counsellor is either fully certified or has a minimum of two years clinical experience. All counsellors have undertaken specific training in delivering the genetic counselling intervention and have access to an intervention protocol manual.

### Study intervention

Development of the intervention was informed by a framework for complex interventions [22]. This enabled the intervention to incorporate the patient-centred ethos and nondirective stance fundamental to genetic counselling practice with a process that is standardised and can be replicated. The intervention was designed to use genetic counselling strategies to address documented personal barriers to family communication. The Reciprocal Engagement Model [23] is the model of genetic counselling practice applied in the intervention, while evidence for barriers was taken from a systematic literature review [1].

The counselling framework for the intervention has three domains; the focus on each is determined by the participant’s needs over time. These are:

• “Getting the picture” about the participant’s experiences of communication to date, including: which relatives have been informed and their responses; recognising and exploring the conscious and unconscious barriers to communication; supporting adjustment of the participant to their own genetic status.

• Forming an intention to act. This includes maintaining or enhancing the participant’s capacity for communication; facilitating decision-making; and resolving ambivalence.

• Planning to act. Here the participant intends to communicate, options are elicited, a plan developed and potential scenarios explored to prepare the participant.

The intervention was designed to be feasible to implement in clinical practice, as an adjunct to usual care [24].

To further emulate the ‘real world setting’ the intervention is delivered by the same genetic counsellor that each participant met at their visit to the genetics clinic.

Intervention phone calls are audiotaped and analysed to examine adherence to the intervention protocol. Such monitoring of the intervention fidelity ensures its delivery and receipt is as intended.

### Process

At the time of their initial genetic consultation all probands receive standard care concerning family communication from the genetic counsellor. This generally involves a discussion of possible implications for other family members and the offer of explanatory letters for the proband to pass on to at-risk relatives Probands are informed about the research study by the genetic counsellor at the end of this consultation. If they consent, their contact details are faxed to the research team for recruitment to proceed. A researcher then contacts potential participants by telephone to explain the project and the possibility that they may receive follow-up telephone calls (if in the intervention arm). Written informed consent is requested by mail and, once received, participants are randomised into the intervention or control group.

Participants who are randomised into the control group receive no further contact specific to family communication.

Participants in the intervention group receive standard care plus three intervention phone calls from a genetic counsellor delivered over the subsequent 12 months.

### Outcomes

#### Primary – measurement of uptake of genetic services

The number of at-risk relatives is ascertained from three generation pedigrees collected by the genetic counsellors at the time of diagnosis for all participants and held in the family Genetics Files. Eighteen months after the proband attends the genetic clinic and is enrolled in the study, the family file is audited to determine the actual number of at-risk relatives who make contact with Victorian genetic clinics.

The total number of at-risk relatives who have contact with a genetics service divided by the total number of at-risk relatives gives a percent that can be compared between the two arms of the study. A person’s ‘at-risk status’ is based on genetic relatedness, taking into account the inheritance pattern for the condition involved. During the study there may be further clarification of the at-risk status. For example, a negative genetic test result for an autosomal recessive condition in one family member means that the mutation will not be further transmitted in that branch of the family. Therefore, the original estimate of the number of ‘at-risk’ relatives will be reduced accordingly. Relatives who live overseas or interstate are excluded from the analysis as we are unable to document their uptake of genetics services.

All data are managed in ACCESS database, 2007 version.

#### Secondary – follow-up telephone interview to assess participant experiences

At the 18 month exit point of the study, participants are telephoned to complete a structured survey assessing their experiences of family communication and participation in a RCT. This identifies differences in attitudes, awareness and suggestions for best practice between the two groups. This survey has been developed using a Delphi process involving the study team and both experienced and student genetic counsellors. It focuses on:

• awareness of the importance of information for at-risk family members

• experience of informing family members

• which family members were informed and when

• the barriers and facilitators to communication

• professional support that is helpful and acceptable to families

• other suggestions for practice.

In addition, the genetic counsellors who delivered the intervention will be interviewed in a focus group setting to reflect on their experience of participation.

A further sub-study to assess fidelity will examine the intervention phone calls to determine counsellors’ adherence to the intervention protocol.

### Sample size

We aim to detect a difference of at least 15% in contact with a genetic service (e.g. 20% of relatives in the control group, 35% in the intervention group). A sample size of 151 at-risk relatives per group has 80% power to detect this difference (with an alpha level of 0.05) if all the at-risk relatives were independent of each other; that is, if the clustering of at-risk relatives is ignored. Data from a preliminary study in Tasmania suggest that there is an average of seven at-risk relatives per proband. With a conservative estimate of five at-risk relatives per proband, a sample size of 151 at-risk relatives requires participation of 30 probands [19].

Since is it probable that responses of at-risk relatives of each proband are more similar to each other than to relatives of other probands, the clustering effect must be taken into account. The average degree of similarity to be expected between at-risk relatives of a given proband (the intraclass correlation (ICC) is unknown as there have been no similar studies. Data from community-based surveys in the UK have shown that many ICCs for households were in the range of 0.0 to 0.3 [25]. Assuming an ICC of 0.25 and an average cluster size of 5, the Design Effect (DE) would be 2 (DE = 1+ (cluster size -1)*ICC). Thus, the required number of at-risk relatives in each group is 302 (=151*2) necessitating a sample size of 60 probands in each arm. Given our conservative assumption of five at-risk relatives per proband, this will detect a difference of at least 15%. In addition, with attrition rate of approximately 15% over the 18 month study period, there is a need to recruit an extra 10 probands for each arm (i.e. 70 probands per arm).

To allow for correlation between the likelihood of making contact with a genetics service of relatives of the same probands, the method of marginal logistic regression models fitted using Generalised Estimating Equations (GEEs) with information sandwich estimates of standard error will be used to estimate the odds ratios between the intervention and control arm for the primary outcome.

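### The design effect of 2 leaves out variation in family size, so the stated 80% power is optimistic if families really average five at-risk relatives

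*Protocol article*

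**What the plan says.** The Sample size section starts from contact rates of "20% of relatives in the control group, 35% in the intervention group" and states: "A sample size of 151 at-risk relatives per group has 80% power to detect this difference", ignoring clustering. It then plans on five relatives per proband: "With a conservative estimate of five at-risk relatives per proband", against an average of seven in a preliminary study. It says the ICC is unknown and that in household surveys "many ICCs for households were in the range of 0.0 to 0.3". It continues: "Assuming an ICC of 0.25 and an average cluster size of 5, the Design Effect (DE) would be 2". From this it derives 302 relatives and 60 probands per arm, raised to 70 for about 15% attrition.

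Two other places determine family size. Under Inclusion criteria a proband need only "have at least one at-risk relative who resides in Victoria". The primary outcome section takes the count from three-generation pedigrees according to inheritance pattern, drops relatives living interstate or overseas, and lowers the count when a branch is later cleared. It defines the outcome as "The total number of at-risk relatives who have contact with a genetics service divided by the total number of at-risk relatives", expressed as a percentage and compared between arms.

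**The concern.** The formula 1 + (m − 1) × ICC holds exactly only when every cluster has size m. Putting an average into it omits a term that grows with the spread of sizes. The spread matters here because a pooled percentage weights each family by its number of relatives, so large families dominate while their members carry overlapping information. A family may enter with one eligible relative, and dominant, recessive and X-linked conditions put different numbers of relatives at risk, so unequal sizes are close to certain.

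At stake is how a null result is read. If the real power is several points below 80%, a non-significant difference is weaker evidence against a 15-point effect than the section implies.

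**Working it through.** **Inputs from the Sample size section:** 20% v 35%; alpha 0.05 (two-sided assumed, since that reproduces the plan's figure); 80% power; mean family size m = 5, with 7 cited; ICC 0.25, cited range 0.0 to 0.3; 60 analysed probands per arm. **Assumption, not in the documents:** the CV of family size, shown at 0.3, 0.5 and 0.8. For orientation, sizes spread evenly from 1 to 9 have mean 5, variance (81 − 1)/12 = 6.67 and CV 2.58/5 = 0.52.

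**Reproducing the plan.** The usual two-proportion formula gives 138 per group, and with the continuity correction 151. So the plan's 151 rests on the corrected formula. DE = 1 + (5 − 1) × 0.25 = 2; 151 × 2 = 302; 302/5 = 60.4, taken as 60. The chain is reproduced.

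**Adding the missing term.**
- Pooled percentage (independence weighting): DE = 1 + ((1 + CV²) × m − 1) × ICC.
- Exchangeable weighting: multiply the equal-size effective n by 1 − CV² × L × (1 − L), where L = m/(m + (1 − ICC)/ICC).
- Effective n per arm for the pooled percentage = 60 × m/DE.
- Uncorrected power = Φ[(0.15√n − 1.96√(2 × 0.275 × 0.725))/√(0.20 × 0.80 + 0.35 × 0.65)]. For corrected power, replace n by n(1 − 1/(0.15n))².

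Example at m = 5, ICC 0.25, CV 0.5:
- Pooled: DE = 1 + (1.25 × 5 − 1) × 0.25 = 2.31; effective n = 300/2.3125 = 129.7; power 73.1% corrected, 77.5% uncorrected.
- Exchangeable: L = 5/(5 + 3) = 0.625; 150 × (1 − 0.25 × 0.234) = 141.2; power 77.0% and 80.9%.

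Power in % (corrected / uncorrected), 60 probands per arm:

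| Mean | ICC | CV | DE, pooled | Pooled | Exchangeable |
|---|---|---|---|---|---|
| 5 | 0.25 | 0 | 2.00 | 79.7 / 83.2 | 79.7 / 83.2 |
| 5 | 0.25 | 0.3 | 2.11 | 77.3 / 81.1 | 78.8 / 82.4 |
| 5 | 0.25 | 0.5 | 2.31 | 73.1 / 77.5 | 77.0 / 80.9 |
| 5 | 0.25 | 0.8 | 2.80 | 63.7 / 69.4 | 72.3 / 76.8 |
| 5 | 0.30 | 0 | 2.20 | 75.4 / 79.6 | 75.4 / 79.6 |
| 5 | 0.30 | 0.5 | 2.58 | 67.9 / 73.0 | 72.8 / 77.3 |
| 7 | 0.25 | 0 | 2.50 | 84.4 / 87.2 | 84.4 / 87.2 |
| 7 | 0.25 | 0.5 | 2.94 | 77.6 / 81.4 | 82.2 / 85.4 |
| 7 | 0.30 | 0 | 2.80 | 79.7 / 83.2 | 79.7 / 83.2 |
| 7 | 0.30 | 0.5 | 3.33 | 71.8 / 76.4 | 77.6 / 81.4 |

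**Where 80% is lost (pooled percentage, ICC 0.25).** At mean 5, the corrected basis has no slack, and the uncorrected basis holds up to a CV of about 0.37. At mean 7, 80% holds up to a CV of about 0.40 corrected and 0.56 uncorrected.

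**Cross-check.** A beta-binomial simulation at mean 5 and ICC 0.25, analysed by a logit-scale Wald test with sandwich errors, gave 84% for equal sizes. At CV 0.6 it gave 76% with independence and 80% with exchangeable weighting. This agrees with the uncorrected formula values.

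**The case against.** The best defence has four parts.

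- **There is no arithmetic slip.** Every figure in the chain is reproduced, and the section speaks of an average of five. Equal sizes are implied by a standard planning formula, not asserted. This stands: the fault is an omitted term.
- **The plan holds a reserve.** It cites a mean of seven and deliberately plans on five, and its ICC of 0.25 lies near the top of the range it quotes. A reader might therefore infer either that the plan is a best case or that the reserve settles the matter. Neither follows. The reserve is real and covers moderate variation at ICC 0.25. But the seven comes from a preliminary study in Tasmania, while this trial counts only relatives in Victoria and may lower the counts later, so it is not assured.
- **The continuity correction is pessimistic.** A Wald test from a GEE would not apply it, so equal families would give about 83%. This stands, and it is why both bases are shown. In particular, ICC 0.30 alone then costs almost nothing against the 80% target (79.6%).
- **The CV is assumed and the working correlation is not stated.** Both are true. The working correlation may properly be left to the full analysis plan. The documents establish that sizes vary, not by how much.

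**Conclusion.** The point holds in a limited form. If the mean is five and the ICC 0.25, any variation in family size makes the design effect larger than 2, and the stated 80% is optimistic. For the pooled percentage at CV 0.5 the loss against equal families is 6.6 points on the plan's corrected basis (79.7% to 73.1%) and 5.7 points without the correction (83.2% to 77.5%). With ICC 0.30 as well, power lies between 68% and 77% across all the bases shown.

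A reader might infer that the trial is underpowered or that 80% is certainly missed. The documents do not support that. With a small CV and no continuity correction, with exchangeable weighting at moderate CV and no correction, or with a mean nearer seven at ICC 0.25, power can stay at or above 80%. The size of the shortfall rests on an assumed CV. That the term is missing does not.

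**What to change.** Restate the power in the Sample size section with DE = 1 + ((1 + CV²) × m − 1) × ICC, or with the exchangeable equivalent if that is the working correlation of the GEE. Take m and the CV from the pedigrees already collected, counting Victorian at-risk relatives only and pooling the arms. This needs no outcome data. Add a small table of power over ICC 0.2 to 0.3, or slightly above, and say whether the continuity correction is used. Leave recruitment unchanged.

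The cost is one recalculated sentence and one table. The downside is that the stated power may become less favourable. If the observed mean is near seven and sizes vary little, it may instead be confirmed.

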### Randomisation

The randomisation sequence was constructed by the Clinical Epidemiology and Biostatistics Unit (CEBU) at the Murdoch Childrens Research Institute using Stata 11.0 (StataCorp, College Station, TX) statistical software. A statistician in CEBU, who is independent of the study investigators, retains the only copy of the randomisation sequence, Randomisation is stratified by genetic counsellor, allocation is 1:1 and random block sizes are used to ensure concealment of allocation. After a participant is enrolled in the study, the study co-ordinator contacts CEBU to obtain the treatment allocation for that participant.

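### Randomisation is stratified by genetic counsellor, but the primary GEE as described names no counsellor term; stating one is a cheap gain if contact rates differ between counsellors

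*Protocol article*

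**What the plan says.** Under Randomisation, the Protocol article states that "Randomisation is stratified by genetic counsellor, allocation is 1:1 and random block sizes are used". The section on the counsellors who deliver the intervention puts their number at 10.

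The primary analysis is in the last paragraph of Sample size. To allow for correlation among relatives of one proband, "the method of marginal logistic regression models fitted using Generalised Estimating Equations (GEEs) with information sandwich estimates of standard error will be used", and the model is to give the odds ratio between arms. The model family, fitting method, standard error, source of correlation and effect measure are therefore all given. Covariates are not mentioned.

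On the sites, Setting and locations says: "These sites were chosen on the basis of variation in client populations and types of genetic diagnoses likely to be made".

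**The concern.** Stratified allocation forces the arms to be balanced within each counsellor's caseload. If counsellor is related to the chance that relatives make contact, that balance makes the true sampling variation of the treatment estimate smaller. A standard error computed without counsellor does not register this and stays at the value suited to unstratified allocation. The test then rejects less often than its nominal level under the null, and the interval is wider than it needs to be.

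Differences between counsellors are plausible here. Sites were picked for varied client populations and diagnoses, and the same counsellor gives usual care to both arms. The family-clustered sandwich estimator deals with correlation within a proband's relatives. It does not take credit for balance across counsellors.

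What is at stake is precision. The article reports recruitment slower than expected (Implication of the hypothesis), so precision that needs no extra probands has some value.

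**Working it through.** **1. The plan's own figures (Sample size).** Inputs: "20% of relatives in the control group, 35% in the intervention group"; two-sided alpha 0.05 (the sidedness is not stated, but two-sided reproduces the figure); power 80%.

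- Pooled formula: n = [1.96 × √(2 × 0.275 × 0.725) + 0.8416 × √(0.16 + 0.2275)]² / 0.15² = 137.9, so 138.
- With continuity correction: (137.9/4) × [1 + √(1 + 4/(137.9 × 0.15))]² = 151.0, the stated 151.
- Design effect: 1 + (5 − 1) × 0.25 = 2; 151 × 2 = 302; 302/5 = 60.4, stated as 60 probands per arm.
- Attrition: 60/0.85 = 70.6, stated as 70.

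The figures reproduce. No step takes credit for stratification.

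**2. Effect of leaving counsellor out.** Simulated setting: 10 counsellors, 6 probands per arm each (60 per arm), 5 relatives per proband, total ICC 0.25. The share ρc of that ICC lying between counsellors is an assumption, varied from 0 to 0.10. The remaining within-family correlation is (0.25 − ρc)/(1 − ρc); at ρc = 0.05 this is 0.20/0.95 = 0.21. There were 2,000 runs per setting, with an uncorrected sandwich standard error clustered on proband. SE and SD refer to the log odds ratio.

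| ρc | Arm-only: mean SE / true SD | Ratio | Arm-only null rejection | Power, arm-only | Power, adjusted, uncorrected SE |
|---|---|---|---|---|---|
| 0 | 0.266 / 0.270 | 0.99 | 6.5% | 84.1% | 85.5% |
| 0.01 | 0.265 / 0.263 | 1.01 | 4.3% | 84.2% | 86.6% |
| 0.02 | 0.265 / 0.257 | 1.03 | 4.8% | 84.5% | 87.8% |
| 0.05 | 0.266 / 0.255 | 1.04 | 4.4% | 85.4% | 89.4% |
| 0.10 | 0.265 / 0.244 | 1.09 | 2.6% | 86.2% | 92.6% |

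The Monte Carlo error of a 5% rejection rate over 2,000 runs is √(0.05 × 0.95/2000) = 0.5 points. The 6.5% arises where counsellors do not differ at all, so omission of counsellor cannot be its cause. A second set of simulations (step 4) found the arm-only test about nominal for shares of 0 to 0.02.

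**3. Why the last column is an upper bound.** The adjusted test with an uncorrected standard error rejected 5.4 to 7.8% under the null. At ρc = 0.05 its mean standard error was 0.260 against a true SD of 0.273 (ratio 0.95).

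**4. With a small-sample-corrected standard error.** Same layout, 3,000 runs per setting. The adjusted test held its level at 4.4 to 5.1%. The arm-only test rejected 3.9% under the null at ρc = 0.05 and 3.3% at 0.10. Against arm-only, adjustment cost at most about 1 point of power at ρc = 0, gained about 2 points at 0.05 and 5 to 6 points at 0.10.

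**5. What the odds ratio then measures.** At ρc = 0.05 the mean log odds ratio was 0.784 without counsellor and 0.844 with it, that is exp(0.784) = 2.19 and exp(0.844) = 2.33. The adjusted coefficient is a within-counsellor (conditional) odds ratio, further from 1 and with a larger sampling SD (0.273 against 0.255). The two are not estimates of one quantity.

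**The case against.** The strongest reply is that the article is silent rather than wrong. It does not call the model unadjusted, and a condensed article may leave covariates to a full protocol or SAP that is not shown. A reader might infer that the primary model contains trial arm only; the text does not say so. What remains is that the paragraph goes down to the type of standard error and the source of correlation, yet passes over the factor used to stratify. Someone working from it alone would omit counsellor.

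Second, the documents contain no figure for variation between counsellors. Varied populations and diagnoses do not prove varied contact rates. This stands: with no such variation there is nothing to gain, which is why the range starts at zero.

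Third, ten strata with 120/10 = 12 analysed probands each, under slow recruitment, may leave some very sparse. This also stands, and the change has to provide for it.

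Three stronger readings are tempting and fail:

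- **Lost power.** A reader might infer that planned power is lost. The calculation never relied on stratification, and the arm-only analysis kept 84 to 86% in simulation.
- **A 7% smaller standard error.** At ρc = 0.05 the variance factor of a family mean falls from 0.40 to 0.35, and √(0.40/0.35) = 1.07. That is linear-model reasoning and does not carry over to the log odds ratio (step 5).
- **Further covariates, or a different reporting scale, as corrections of error.** The Background remarks that "Women are more likely to communicate than men [16] and, when communication occurs, it appears that first-degree relatives are usually informed first". That concerns who communicates and who is told first, not who contacts a clinic, and neither sex nor relatedness is a stratification factor. Nor does the article commit to reporting an odds ratio alone, since Outcomes also provides for comparing percentages. These are preferences.

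**Conclusion.** The point holds as a minor one. Allocation is stratified by counsellor, and the described primary GEE accounts only for clustering within proband. If contact rates differ between counsellors, an analysis without counsellor is conservative and forgoes some precision. It does not inflate the false-positive rate, and the planned 80% power stands.

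The gain from adjustment with a corrected standard error is about 0 to 6 power points for assumed counsellor shares of the ICC from 0 to 0.10, with a possible loss of about 1 point if counsellors do not differ. These figures assume equal caseloads, five relatives in every family, a total ICC of 0.25 and counsellor effects that are normal on the logit scale. The direction is secure; the size is not, because the documents give no between-counsellor variance.

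**What to change.** State, before analysis, that the primary GEE includes trial arm and genetic counsellor as a fixed factor, clustered on proband, with a named small-sample-corrected sandwich standard error. The correction is needed because the uncorrected estimator is slightly liberal once the counsellor terms are added. Fix in advance a rule for pooling counsellors with very few probands by site. Obtain the marginal treatment effect by standardisation from this same model, with its standard error from that model, so that adjustment does not silently replace a marginal odds ratio with a conditional one. If a fuller protocol or SAP already includes counsellor, it is enough to say so.

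The cost is analysis wording only. Each proband's counsellor is already known, because allocation depended on it, and sample size and data collection do not change. The downsides are the possible pooling of sparse strata and a loss of up to about 1 point of power if counsellors turn out not to differ.
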